## Methods

### Study design

The HEPAR PLUS study is a single centre, interventional, non-randomized, non-comparative, open label study. In this phase 2 study all patients will receive additional ^166^Ho-RE after ^177^Lu-DOTATATE. Overall, 30–48 patients with metastasized NET will be investigated for efficacy and toxicity.

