### Statistical analysis

This single arm open label study will have a sequential design. Stopping boundaries are determined such that an overall one-side alpha of at the most 0.05 is maintained in case the true tumour response is 20%. Early termination at a response interim analysis (after 30, 36 or 42 patients) is determined by pre-defined boundaries on the number of partial and complete responses according to RECIST 1.1 (Table 4). A superiority or futility boundary may be reached or crossed before 30 patients are reached, but the study will continue to at least 30 patients to allow estimation of the key secondary endpoints. The sequential design with boundaries as given in Table 4 will have a power of 90% to reach a positive tumour response decision in case the true target lesions tumour response is 40%. The exact overall one-sided type I error is 4.5%.

**Table 4 Tab4:** Stopping boundaries for early termination at interim analysis

Analysis	Sample Size	Lower boundary	Upper boundary
1	30	5	11
2	36	6	13
3	42	7	14
4	48	15	16

Interim analysis of toxicity with descriptive statistics (N, mean, median, etc.) will be performed for every 3 patients. All analysis will be performed in the Full Analysis Set (FAS), including all patients who received at least the scout dose procedure (see below). The Per Protocol Set (PPS) will include all patients who complied with the protocol up to at least 3 months. PPS analyses will be used for the primary endpoint. For the assessment of the primary objective at least 30 patients should have a 3 months follow-up CT-scan. If patients do not reach the 3 months follow-up CT-scan or receive a new treatment prior to the evaluation moment, a new patient will be included for the PPS analysis.

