##### Withdrawal of individual patients

Patients may be withdrawn from the study if a serious adverse event occurs.

Patients will be withdrawn from the study if 1) the investigator considers it in the best interest of the patient that he/she be withdrawn (e.g. progressive disease), 2) the patient withdraws consent or 3) the patient is unable to comply with the protocol procedures.

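### Primary response is analysed per protocol, with patients lacking the 3-month CT or newly treated replaced and not scored as non-responders, so the 4.5% type I error is not guaranteed for all treated patients

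*Protocol article*

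**What the plan says.** All the main statements are in the protocol article, under Statistical analysis.

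- **Design claim.** Boundaries are set so that "an overall one-side alpha of at the most 0.05 is maintained in case the true tumour response is 20" per cent. The section adds "The exact overall one-sided type I error is 4.5" per cent, and a "power of 90% to reach a positive tumour response decision in case the true target lesions tumour response is 40" per cent. Table 4 gives lower/upper boundaries of 5/11, 6/13, 7/14 and 15/16 responses at 30, 36, 42 and 48 patients.
- **Analysis sets.** One sentence reads "All analysis will be performed in the Full Analysis Set (FAS"; that set starts at the scout dose. Two sentences later: "PPS analyses will be used for the primary endpoint". The per-protocol set (PPS) requires compliance to at least 3 months.
- **Replacement.** "If patients do not reach the 3 months follow-up CT-scan or receive a new treatment prior to the evaluation moment, a new patient" is included for the PPS analysis.
- **Withdrawal.** Under Withdrawal of individual patients, one ground is that "the investigator considers it in the best interest of the patient that he/she be withdrawn (e.g. progressive disease". Withdrawn consent and inability to comply are the others.
- **Size.** Under Study design: "Overall, 30–48 patients with metastasized NET will be investigated for efficacy and toxicity". It is not said whether replaced patients count towards the 48.

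The article does not say how a replaced patient is scored, or whether the 20% and 40% are rates among treated or evaluable patients.

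**The concern.** Membership of the primary analysis set depends on what happens after treatment. A patient given a new treatment before the 3-month scan, or withdrawn for progression before it, is unlikely to have been heading for a complete or partial response. Taking such patients out and drawing new ones removes probable failures from the denominator.

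The resulting counts go into Table 4, which can stop the trial and declare a positive result. Any bias is therefore in the favourable direction, on the decision itself. Because the study is open label with a single arm, the choice to withdraw or re-treat is made with knowledge of how the patient is doing. The estimate becomes response among those who reached the scan without other treatment, whereas a reader is likely to take it as response among those treated.

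**Working it through.** **Inputs from the article (Statistical analysis, Table 4).** Looks at n = 30, 36, 42, 48; success at ≥ 11, 13, 14, 16 responses; futility at ≤ 5, 6, 7, 15; null rate 0.20; alternative 0.40.

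**Step 1: reproduce the stated figures.** An exact binomial recursion carries the distribution of responses from look to look and removes the paths that cross a boundary.

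- At p = 0.20, the chance of success at the four looks is 0.0256 + 0.0048 + 0.0113 + 0.0035 = 0.0452 (stated 4.5%).
- At p = 0.40, the total is 0.898 (stated 90%).

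Both reproduce, so the boundaries are sound. A reading in which the upper boundary must be exceeded gives 0.0197 and 0.827, which does not match.

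**Step 2: model replacement.** Two quantities are not in the article and are assumed: d, the share of treated patients replaced, and r, the response rate those patients would have had. With a true rate of 0.20 among all treated, the rate among analysed patients is

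p = (0.20 − d·r) / (1 − d).

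For example, d = 0.10 and r = 0 gives 0.20/0.90 = 0.222; d = 0.10 and r = 0.10 gives 0.19/0.90 = 0.211. The chance of a positive decision with Table 4 unchanged is:

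| Replaced (d) | Analysed rate, r = 0 | Type I error, r = 0 | Analysed rate, r = 10% | Type I error, r = 10% | Type I error, r = 20% |
|---|---|---|---|---|---|
| 5% | 21.1% | 6.5% | 20.5% | 5.4% | 4.5% |
| 10% | 22.2% | 9.3% | 21.1% | 6.6% | 4.5% |
| 15% | 23.5% | 13.3% | 21.8% | 8.1% | 4.5% |
| 20% | 25.0% | 18.9% | 22.5% | 10.1% | 4.5% |

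**Step 3: where the 0.05 ceiling is passed.** The error reaches 0.05 at an analysed rate of about 0.2028.

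- With r = 0: d = 1 − 0.20/0.2028 ≈ 1.4%.
- With r = 10%: d = (0.2028 − 0.20)/(0.2028 − 0.10) ≈ 2.7%.

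Out of 48 patients these are 0.7 and 1.3 patients.

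**Step 4: effect on the estimate.** At the first look, 11/30 = 36.7% meets the upper boundary. If three patients had been replaced and were counted as failures, the rate would be 11/33 = 33.3%.

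**Step 5: the alternative rule.** If every treated patient is counted and a missing or post-new-treatment assessment is a non-response, the error at a true 20% is 4.5% and power at a true 40% is 89.8%, whatever the loss. If 40% is instead the rate among evaluable patients, the rate among treated is 0.40 × (1 − d): 0.38 at d = 5% (power 84.1%) and 0.36 at d = 10% (power 76.5%).

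**The case against.** Three stronger readings are tempting, and the article supports none of them.

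**All early progressors and deaths are dropped.** The trigger is the absence of a 3-month CT, or new treatment before it. A patient who progresses but has that CT, without withdrawal or new treatment, stays in as a non-responder. Under Follow-up visits, CT is scheduled at 3, 6, 9 and 12 months, so progression before the endpoint scan would have to show clinically or on unscheduled imaging. Deaths are not named; it is inferred that a patient who dies before 3 months does not reach the scan.

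**The 4.5% is wrong.** If the 20% means evaluable patients, 4.5% is correct for that narrower quantity. It also holds if replaced patients would respond as often as the rest. Some replacements may indeed be unrelated to outcome, such as withdrawn consent or a scout dose not followed by treatment.

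**Heavy losses are to be expected because entry requires a life expectancy of only > 12 weeks.** That is an eligibility floor and not a forecast. The article cites a median survival of 46 months after PRRT (Background) and 25 months with extensive liver involvement (Table 1), and it excludes liver involvement above 70%. Nothing in it supports 15% or 20% replaced; those rows only show the range.

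The two sentences on analysis sets can also be read as a general rule with an exception. They still need reconciling, but they are not themselves evidence of bias.

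What remains is that replacement for new treatment is an explicit rule, that withdrawal for progression can lead to a missing CT, and that nothing scores either as non-response. A condensed article does not explain this away, because the rule is stated.

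**Conclusion.** The point holds in conditional form. The boundaries are correctly calculated. The primary set and the replacement rule mean that the stated error is not guaranteed for response among all treated patients. The bias is upward whenever replaced patients respond less often than the rest, which is plausible for at least two of the routes (new treatment and withdrawal for progression).

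Its size cannot be fixed from the article. With 5% to 10% replaced, the error is 5.4% to 6.6% if one in ten of them would respond, and 6.5% to 9.3% if none would. The margin is thin: one or two outcome-related replacements are enough to pass 0.05 under these assumptions. All these figures assume a true 20% response among all treated patients and use Table 4 unchanged.

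**What to change.** 1. Make the primary response analysis, and the counts entered in Table 4, cover all patients who received the therapeutic 166Ho-RE.
2. Count as non-response any such patient with no 3-month CT, for whatever reason (including death or withdrawal for progression), or with new treatment before it.
3. Limit replacement to patients who had the scout dose but not the treatment dose.
4. Keep the PPS as a sensitivity analysis, and rewrite the sentence assigning all analysis to the full analysis set so that it agrees with the set named for the primary endpoint.
5. State that the 20% and 40% are response rates among treated patients.

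The change is to wording only; the boundaries stay as they are. The cost is power if the 40% was meant for evaluable patients: from 89.8% to about 84% with 5% non-evaluable, or 76% with 10%. If 40% is a reasonable target among treated patients, there is no loss.

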### Monitoring

All safety interim analyses will be presented to our Independent Data Monitoring Commission (IDMC), consisting of one interventional radiologist, one nuclear medicine physician, one gastroenterologist and one biostatistician. All IDMC members are not involved in the trial and have no conflicting interests. Additionally, safety analysis will be performed every 3 months during the recruitment of the first 30 patients, after patient 36, patient 42 and patient 48, and evaluated by the IDMC.

Severe adverse (device) events will be reported to the Ethics Committee of the University Medical Center Utrecht and IDMC within 8 days. In accordance with Dutch regulations on research with medical devices, a summary of all severe adverse (device) events will be reported to the Dutch Health Care Inspectorate (in Dutch: Inspectie GezondheidsZorg en Jeugd in oprichting; IGJ) every 3 months.

### Data management

All patient data collected in this trial, will be coded. All coded data will be entered in to an, in-house developed, electronic case report form (e-CRF) in a secure digital environment. All collected data is monitored and validated by an independent, external data monitor approximately every 3–4 months. In accordance with Dutch regulations, all collected data will be stored for a duration of 15 years. Trial data is only accessible to the study physician, principal investigator and external data monitor.

### Ethical considerations

The study protocol has been approved by the Ethics Committee and the institutional radiation protection committee of the University Medical Centre Utrecht, the Netherland. This study will be performed in accordance with the Declaration of Helsinki (current version October 2013), the Medical Research Involving Human Patients Act (WMO, the Netherlands) and the requirements of International Conference on Harmonization (Good Clinical Practice). In accordance to regulations, all future protocol amendments need Ethics Committee approval. Unexpected harm to the participant during the trial, is covered by the institutions’ insurance for clinical trials.

### Treatment

#### Screening

After obtaining informed consent, all study proceedings will occur in the University Medical Center Utrecht, Utrecht, The Netherlands. A screening visit will take place at the outpatient clinic prior to the first angiography. The study physician and principal investigator will check in- and exclusion criteria, perform a physical examination (including blood pressure, temperature and heart rate) and assess the WHO performance status of the patient. All patients are asked to fill out the European Organization for Research and Treatment of Cancer (EORTC) QLQ-C30 and QLQ-GINET21 questionnaires. Additional tests include relevant laboratory testing (haematology, coagulation profile and serum chemistry) including a tumour marker (when present/measurable in the patient), electrocardiogram (ECG) and a contrast-enhanced CT. All contrast enhanced CT’s will be assessed by RECIST 1.1 criteria [23].

#### Angiography

Patients are admitted for 3 days (2 nights) starting the day prior to the angiography. After physical examination and relevant laboratory testing, patients are pre-hydrated to prevent kidney damage, and started on proton pump inhibitors for 6 weeks (pantoprazole once a day 40 mg). Premedication 1 h prior to the angiography consists of one dose of corticosteroids, antihistamines and anti-emetics (respectively dexamethasone 10 mg, clemastine 1 mg and ondansetron 8 mg), at the same time a tranquilizer is offered to the patient (oxazepam 10 mg). If the patient is familiar with a mild to moderate contrast allergy, additional corticosteroids and antihistamines will be given prior to the angiography according with national guidelines of the Central Accompaniment Institution (CBO in Dutch) [24].

A skilled and trained interventional radiologist will perform all angiographies of the upper abdominal vessels. A catheter is introduced via one of the femoral arteries by the Seldinger technique. After identifying all arteries supplying the liver, additional branches of these arteries that supply other organs than the liver are coiled, if needed. This usually involves the gastroduodenal artery (GDA) and right gastric artery (RGA).

#### Scout dose

Once successful identification of the supplying arteries and occlusion of additional branches has been performed, a scout dose of 250 MBq ^166^Ho-microspheres will be administered [20, 25]. Due to the photon emission of ^166^Ho, distribution of the microspheres, lung shunting and extrahepatic depositions can all be assessed using SPECT/CT. Planar imaging and SPECT/CT will be performed following the angiography and evaluated qualitatively as well as quantitatively. Extrahepatic deposition of activity is a contra-indication for treatment. Lung shunting will be assessed by planar imaging and SPECT/CT and should not exceed the maximum tolerable lung absorbed dose (i.e. 30 Gy).

#### Treatment

If the pre-treatment assessment is successful, patients return to the angiography suite for the treatment angiography combined with the ^166^Ho-RE. This will take place on the same day as the pre-treatment angiography and scout dose procedure (see Fig. 3). Based on the results of the dose escalation study (i.e. HEPAR I trial), a whole liver absorbed dose of 60 Gy was determined to be safe. A whole liver absorbed dose of 60 Gy leads to the following equation for activity calculation:$$ {A}_{{}^{166} Ho}(MBq)=3781\ \left( MBq\ast \frac{Gy}{J}\right)\ast liver\ weight\ (kg) $$

**Fig. 3 Fig3:**
[figure not shown]
Study protocol depicting the time line and study proceedings between inclusion and hospital discharge

As mentioned above, additional information derived from the scout dose SPECT/CT can change treatment planning, either performing a one session whole liver treatment or two session sequential whole liver treatment. A significant lung shunt dose (> 30 Gy) will lead to a reduction in treatment activity.

#### Radiation exposure rate

The radiation exposure rate of the patient will be measured from 1-m distance at *t* = 0 h and *t* = 24 h after the ^166^Ho-RE.

#### Follow-up

##### Follow-up visits

During 12 months after treatment, patients are followed at the outpatient clinic. The visits will take place after 3 weeks, 6 weeks, 3 months, 6 months, 9 months and 12 months (closing visit). During these visits patients will undergo a physical examination, laboratory testing, WHO performance status assessment and will be monitored for (serious) adverse (device) events. Prior to the 3 weeks, 6 weeks and 3 months visits, patients are asked to fill out the EORTC questionnaires (QLQ-C30 and QLQ-GI.NET21). Prior to the 3, 6, 9 and 12 months visits, a CT will be performed for response assessment according to the RECIST 1.1 criteria.

##### Primary objectives

Two distinct objectives are the focus of our study. Tumour response on CT at 3 months of follow-up will be the first primary objective. This is defined as complete response (CR = disappearance of all lesions) or partial response (PR = ≥30% decrease in the sum of the longest diameters of the target lesions, compared to baseline measurements). The second primary objective is to establish the safety and toxicity profile of treatment with ^166^Ho-RE as an additional treatment after ^177^Lu-DOTATATE, using the Common Terminology Criteria for Adverse Events (CTCAE version 4.03) [26].

##### Secondary objectives

Three secondary objectives have been defined. Anti-tumour effect will be assessed by relevant tumour markers (when available), expressed as a percentage of the pre-treatment values. Furthermore, Quality of Life (QoL) will be assessed using the EORTC questionnaires (QLQ-C30 and QLQ-GI.NET21) during the first 3 months after treatment. The impact of treatment on QoL will be compared to tumour response and other parameters.

Additionally, biodistribution and dosimetry will be evaluated using a dual isotope fusion SPECT/CT protocol. After the standard scout dose SPECT/CT and treatment dose SPECT/CT (i.e. ^166^Ho-SPECT), 50 MBq of ^99m^Tc-phytacis (CIS bio, France) will be administered. Subsequently a dual-isotope SPECT/CT will be acquired, simultaneously providing a ^166^Ho-SPECT for assessment of microsphere distribution and a ^99m^Tc-phytacis SPECT for the assessment of truly functional liver parenchyma.

##### Safety profile

The phase 1 study on ^166^Ho-RE (HEPAR I trial) [20] and its subsequent phase 2 study (HEPAR 2 trial) [27], demonstrated similar treatment-related effects as the current commercially available ^90^Y-microspheres. Common adverse events up to grade 1 or 2 of the CTCAE v4.03 included: fever, nausea, vomiting, abdominal discomfort, and fatigue, often called the post-embolization syndrome. These complaints were generally self-limiting within 4–6 weeks. More serious adverse events of RE in general were rare (< 1%) and included RE-induced liver disease (REILD) [28] and inadvertent extrahepatic distribution of activity [29].

##### Escape medication

The protocol ensures all patients are pre- and post-hydrated in order to minimize the chance of renal insufficiency caused by the vascular contrast agent, jodixanol (Visipaque®). After ^166^Ho-RE standard escape medication includes paracetamol up to 4000 mg / day and ondansetron up to 24 mg, as respectively oral analgesic and intravenous anti-emetic. If persisting nausea occurs, additional metoclopramide up to 120 mg / day will be used. In case of diarrhoea, patients will receive loperamide up to 16 mg / day. In this specific patient group, some patients might experience excessive release of NET-related hormones that could cause a ‘carcinoid syndrome’ or ‘carcinoid crisis’. These complaints can be prevented (to some extent) with octreotide intravenously, steroids and hydration.

##### Withdrawal of individual patients

Patients may be withdrawn from the study if a serious adverse event occurs.

Patients will be withdrawn from the study if 1) the investigator considers it in the best interest of the patient that he/she be withdrawn (e.g. progressive disease), 2) the patient withdraws consent or 3) the patient is unable to comply with the protocol procedures.

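### Withdrawal for a serious adverse event or progression is not separated from outcome follow-up, so toxicity can be truncated and early progressors replaced in the response analysis, while the analysis set for toxicity is left ambiguous

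*Protocol article*

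**What the plan says.** **Withdrawal.** The section Withdrawal of individual patients has two rules. One is permissive: "Patients may be withdrawn from the study if a serious adverse event occurs". The other is mandatory and applies, among other grounds, if "the investigator considers it in the best interest of the patient that he/she be withdrawn (e.g. progressive disease"). The section does not mention follow-up after withdrawal.

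**Follow-up.** "During 12 months after treatment, patients are followed at the outpatient clinic", with visits at 3 and 6 weeks and at 3, 6, 9 and 12 months. These cover laboratory tests and adverse events, with CT from month 3 onwards (Follow-up visits).

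**Objectives.** Tumour response on the 3-month CT is the first primary objective. For the other: "The second primary objective is to establish the safety and toxicity profile of treatment" (Primary objectives). The abstract also lists both as primary.

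**Analysis sets.** The Statistical analysis section first says: "All analysis will be performed in the Full Analysis Set (FAS), including all patients who received at least the scout dose procedure". It then says: "The Per Protocol Set (PPS) will include all patients who complied with the protocol up to at least 3 months". Next comes: "PPS analyses will be used for the primary endpoint", followed by: "For the assessment of the primary objective at least 30 patients should have a 3 months follow-up CT-scan". A patient who does not reach that CT, or who starts a new treatment before it, is replaced by a new patient for the PPS analysis.

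**The concern.** Once a patient has been treated, leaving the study mainly ends measurement. A rule that makes a serious adverse event or progression a reason to leave therefore lets the outcome decide who continues to be observed. Two things are at stake.

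- **Toxicity.** The Discussion itself raises concern about cumulative radiation dose, the short interval after PRRT and radioembolization-induced liver disease. The patients whose course matters most for that question are those the rule allows to leave.
- **Response.** Early progressors are non-responders. If they leave before the 3-month CT and are replaced, the responder count is compared with the stopping boundaries in a selected group.

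The analysis-set wording adds to the problem. There are two primary objectives but one primary endpoint in the sentence that assigns the PPS, and no sentence names the set for toxicity.

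**Working it through.** **1. Toxicity: the relevant sections side by side.**

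- In the FAS, an event that leads to withdrawal is already recorded and still counts. What can be lost is what follows: worsening to a higher grade, resolution, and new events up to month 12.
- Reporting severe events to the Ethics Committee and the monitoring committee within 8 days (Monitoring) captures that an event occurred, not its later course.
- The size of this loss cannot be calculated, because the article gives no withdrawal rate.

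**2. Response: the plan's own figures first.**

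Inputs are from Table 4: looks at n = 30, 36, 42, 48; lower boundaries 5, 6, 7, 15; upper boundaries 11, 13, 14, 16. An exact binomial recursion carries forward the distribution of responders among trials not yet stopped. The decision is positive if responders are at or above the upper boundary and negative if at or below the lower.

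- True response 20%: 0.0256 + 0.0048 + 0.0113 + 0.0035 = 0.0452, against 4.5% stated.
- True response 40%: 0.7085 + 0.0694 + 0.0899 + 0.0301 = 0.8979, against 90% stated.

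The design figures reproduce.

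**3. Response: effect of replacing early progressors.**

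Assume a fraction d of all treated patients are non-responders who leave before the 3-month CT and are replaced. With a response rate of 20% in all treated patients, the rate in the PPS is 0.20 / (1 − d). Putting that rate through the same recursion gives:

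| d (assumed) | PPS response rate | Chance of a positive decision |
|---|---|---|
| 0 | 20.0% | 4.5% |
| 5% | 0.20/0.95 = 21.1% | 6.5% |
| 10% | 0.20/0.90 = 22.2% | 9.3% |
| 15% | 0.20/0.85 = 23.5% | 13.3% |
| 20% | 0.20/0.80 = 25.0% | 18.9% |

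Every row with d above zero exceeds the plan's one-sided limit of 0.05. At d = 10%, the number involved is 3 in 30 treated patients.

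**4. Toxicity: what the ambiguity could cost.**

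This applies only if toxicity were summarised in the PPS. With a true serious-toxicity rate t and a fraction w of those patients withdrawn before 3 months, the PPS rate is t(1 − w) / (1 − tw). Both inputs are assumed.

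| t | w = 25% | w = 50% |
|---|---|---|
| 10% | 7.7% | 5.3% |
| 15% | 11.7% | 8.1% |
| 20% | 15.8% | 11.1% |

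In the FAS the rate of the triggering event stays at t.

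**The case against.** The strongest reply is that the plan already puts all analysis in everyone who received at least the scout dose procedure. The PPS sentence speaks of one endpoint, and the sentences after it concern the 3-month CT. On that reading toxicity belongs to the FAS, and no replacement can displace a patient who had an event. This stands, and it limits the point. A reader might infer that patients with toxicity are dropped from the toxicity analysis, but no sentence places toxicity in the PPS.

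Other replies have some force:

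- Withdrawal for a serious adverse event is optional, and progression is only an example under a best-interest clause. Neither is an automatic exit.
- Treatment is not always complete on day one. A scout dose comes first and two sessions are possible, so withdrawal may stop further exposure. The point is therefore confined to follow-up of patients already treated.
- No CT is scheduled between screening and month 3. Only progression recognised clinically or on unscheduled imaging can remove a patient before the response assessment, so d may be small.
- The Safety profile section calls more serious events of radioembolization rare (below 1%). That describes radioembolization in general, whereas the toxicity objective here concerns its use soon after PRRT.
- The full protocol may provide for follow-up after withdrawal. If so, that part is settled by saying so. The conflict over analysis sets and the replacement rule are stated in the article itself.

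**Conclusion.** The point holds in a limited form, with three parts.

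1. The withdrawal rule, followed as written, can cut off later events, worst grade and resolution for a primary objective, whichever analysis set is used. The size is unknown.
2. Withdrawal for progression before 3 months, combined with replacement, inflates the response rate. The type I error rises from 4.5% to about 9.3% if 10% of treated patients are replaced non-responders, with a range of 6.5% to 18.9% for 5% to 20%. This assumes that the 20% reference rate applies to all treated patients and that everyone replaced for this reason is a non-responder. The article supplies no rate for d.
3. The analysis set for toxicity is ambiguous, because the general FAS rule and the PPS rule for the primary endpoint are not reconciled with two primary objectives.

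It would go too far to say that the plan removes patients with toxicity from the toxicity profile. The roughly halved rates in the last table arise only if toxicity is read in the PPS and half of the affected patients leave before 3 months.

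**What to change.** Four statements, in the withdrawal and statistical sections:

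- A serious adverse event or progression does not end data collection. Every patient who received any ¹⁶⁶Ho stays in the scheduled follow-up for adverse events, laboratory tests and CT unless consent for follow-up is withdrawn.
- Toxicity is analysed in the FAS.
- The PPS and the replacement rule apply only to the CT response analysis.
- A patient who progresses before the 3-month CT counts as a non-responder and is not replaced. The minimum of 30 assessed patients should be worded so that it includes such patients.

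Decisions on stopping further treatment are left unchanged; only observation and analysis are affected. The cost is protocol wording, a few more visits that are already scheduled, and possibly less favourable toxicity and response figures. The article describes recruitment as ongoing, and follow-up that is missed may not be recoverable at analysis, so the change is best made during recruitment.
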